### Withdrawal from Study

Subjects will be withdrawn from the study at their request, without prejudice, as documented and explained at the time of consenting. Patients who withdraw will be asked to consent to follow-up testing for the remainder of the trial to enable an intention to treat data analysis.

### Power calculation

Resource limitations will allow us to recruit 66 patients within a two-year period. Data from other studies indicates that Pentraxin 3 has the highest variability of the three outcome measures (mean ± SD; isoprostanes = 54.1 ± 7.0 [46], PWV = 11.4 ± 2.4 [47], pentraxin 3 = 0.75 ± 0.3 [48]). We assume that a decrease of 10% in pentraxin 3 would be clinically significant. Therefore, with alpha = 0.05, we will have about a 17% power to detect this 10% change in pentraxin 3 and a 52% power to detect a 20% change. This also allows for a 20% withdrawal rate. We recognize that the power of the study is small, but believe that the study will form the basis for progression to a larger study.

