**Method and Design:**

This is a randomised, placebo controlled clinical trial. A total of 66 renal transplant recipients will be enrolled and allocated to receive either 12 mg/day of astaxanthin or an identical placebo for one-year. Patients will be stratified into four groups according to the type of immunosuppressant therapy they receive: 1) cyclosporine, 2) sirolimus, 3) tacrolimus or 4) prednisolone+/-azathioprine, mycophenolate mofetil or mycophenolate sodium. Primary outcome measures will be changes in 1) arterial stiffness measured by aortic pulse wave velocity (PWV), 2) oxidative stress assessed by plasma isoprostanes and 3) inflammation by plasma pentraxin 3. Secondary outcomes will include changes in vascular function assessed using the brachial artery reactivity (BAR) technique, carotid artery intimal medial thickness (CIMT), augmentation index (AIx), left ventricular afterload and additional measures of oxidative stress and inflammation. Patients will undergo these measures at baseline, six and 12 months.

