### Primary Objectives and Primary Outcome Measures

The primary objectives are to assess the effects of astaxanthin on arterial stiffness, oxidative stress and inflammation. The primary outcome measures will be outlined below. The hypotheses are that astaxanthin will significantly improve the rates of change in these measures compared with controls.

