### Statistical analysis

All baseline continuous variables between groups will be compared using general linear modelling, whilst categorical variables will be compared using exact logistic regression. The rates of change will be estimated for each patient separately by linear regression. General linear modelling, will be used to compare the mean rate of change in primary outcome measures between groups, unadjusted and adjusted for actual and potential confounding variables. Mean differences, 95% confidence intervals and P-values will be corrected for repeated measures, and P-values corrected for multiple comparisons by the Holm method. All analyses will be performed using Stata/IC 10.1 for Windows (StataCorp LP, College Station, Tx).

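### The stated power (17%/52%) uses the SD of a single pentraxin 3 level, but the primary analysis compares rates of change; it carries over only if the baseline to 12-month correlation is about 0.5, or about 0.6 if 20% of patients are lost

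*Protocol article*

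**What the plan says.** Under Power calculation, the protocol article fixes the sample size by feasibility: "Resource limitations will allow us to recruit 66 patients within a two-year period". It then takes published means and SDs for the three primary outcomes, stating "Data from other studies indicates that Pentraxin 3 has the highest variability of the three outcome measures" and listing among them "pentraxin 3 = 0.75 ± 0.3", and sets the target effect: "We assume that a decrease of 10% in pentraxin 3 would be clinically significant". The result is given as "with alpha = 0.05, we will have about a 17% power to detect this 10% change in pentraxin 3", with 52% power for a 20% change. The same paragraph adds that a withdrawal rate of 20% is allowed for, and concedes that the power is small.

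The analysis is of a different quantity. Under Statistical analysis, a rate of change is estimated for each patient by linear regression, and a general linear model is used to "compare the mean rate of change in primary outcome measures between groups", both unadjusted and adjusted. The hypothesis under Primary Objectives and Primary Outcome Measures has the same form: "astaxanthin will significantly improve the rates of change in these measures compared with controls". The Abstract (Method and Design) puts the measurements at baseline, six and 12 months.

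**The concern.** A mean of 0.75 is a level of pentraxin 3, so the 0.3 beside it is read as the spread between patients at one time. Power for a comparison of slopes depends on the spread of slopes. That spread is larger or smaller than 0.3 according to how strongly a patient's 12-month value follows the baseline value. The protocol fixes the power inputs on one scale and the primary comparison on another, and gives nothing that links them.

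What is at stake is whether the stated power describes the planned test. It could be too high or too low. The withdrawal allowance adds a second uncertainty, because the figures match a calculation in which no patient is lost.

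**Working it through.** **Inputs from the protocol article.** Power calculation: 66 patients; pentraxin 3 mean 0.75, SD 0.3; alpha 0.05; changes of 10% and 20%; withdrawal 20%. Statistical analysis: the outcome is each patient's slope. Abstract: visits at 0, 6 and 12 months.

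**Assumptions.** Allocation 1:1, so 33 per arm (two arms, but no ratio is stated); a two-sided test (sidedness is not stated); equal SD at baseline and 12 months; an unadjusted slope comparison. The baseline to 12-month correlation ρ is not in the document, so every value of it below is assumed.

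**Step 1: reproduce the stated power.** The differences are 0.10 × 0.75 = 0.075 and 0.20 × 0.75 = 0.15. For a two-sample t test the noncentrality is δ / (SD × √(2/n)).

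- n = 33 per arm, SD 0.3: noncentrality 1.016 and 2.031; power 17.0% and 51.6%. These are the stated 17% and 52%.
- n = 26 per arm (33 × 0.8 = 26.4), SD 0.3: power 14.3% and 42.4%.
- One-sided tests (normal approximation) give 26.5%/65.0% with 33 per arm and 22.9%/56.3% with 26; a one-sample test with n = 33 gives 28.6%/79.5%. None of these matches.

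So the figures rest on the level SD of 0.3 and on all 33 patients per arm.

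**Step 2: the SD of the planned outcome.** With times 0, 0.5 and 1 year, the deviations from the mean time are −0.5, 0 and 0.5, and their sum of squares is 0.5. The least-squares weights are therefore −1, 0 and +1 per year. For a patient with all three visits, the slope is month 12 minus baseline, and the six-month value drops out. With equal SDs,

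SD(slope) = 0.3 × √(2(1 − ρ)).

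This equals 0.3 when 2(1 − ρ) = 1, that is at ρ = 0.5.

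**Step 3: power for the slope comparison** (noncentral t, two-sided 0.05; each cell is the power for a 10% / 20% change).

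| Assumed ρ | SD of slope | 33 per arm | 26 per arm |
|---|---|---|---|
| 0.3 | 0.355 | 13.5% / 39.4% | 11.6% / 32.1% |
| 0.5 | 0.300 | 17.0% / 51.6% | 14.3% / 42.4% |
| 0.6 | 0.268 | 20.1% / 60.9% | 16.7% / 50.7% |
| 0.7 | 0.232 | 25.2% / 73.3% | 20.7% / 62.6% |
| 0.8 | 0.190 | 35.3% / 88.5% | 28.7% / 79.8% |

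**Step 4: the ρ that returns the stated power.** With 33 per arm, 17% needs ρ = 0.499 and 52% needs ρ = 0.505; any ρ from about 0.48 to 0.525 gives the 52% within 2 points. With 26 per arm the values are 0.609 and 0.613 (about 0.60 by the normal approximation).

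**The case against.** The best defence is that nothing has been miscalculated. The figures reproduce, the sample size was set by resources and not by power, and the protocol says openly that power is small. Without ρ, no direction of error can be shown: with all 66 patients analysed and ρ above 0.5, the stated power is conservative. An article may also leave the correlation to a fuller document. Much of this stands. There is no arithmetic slip, and no value of ρ would change enrolment or conduct. But the point is not that a detail is missing. The article itself fixes both the power inputs and the slope analysis, and the two do not match. Conceding low power does not make the figure right for the planned test.

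Three stronger readings are tempting, and the document does not support them.

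- A reader might infer that the power holds only if ρ is exactly 0.5. That value requires all 66 patients with complete data, equal SDs and an unadjusted slope. A narrow band around it returns the rounded figures, and with 26 per arm about 0.6 is needed.
- A reader might infer that ranking pentraxin 3 as the most variable outcome is wrong. The effects are percentages of the mean, so the coefficient of variation is a reasonable scale, and it supports the sentence: 0.3/0.75 = 40%, against 2.4/11.4 = 21% and 7.0/54.1 = 13%.
- A reader might infer that a larger trial would be planned from this power figure. The article says only that the study, or its data, may lead to one.

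On withdrawal, the Withdrawal from Study section asks patients who stop to consent to further testing. If they all did, 33 per arm could be right. The power paragraph does not say that this is how its allowance works.

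**Conclusion.** The concern holds as a mismatch between the power statement and the planned analysis. The 17%/52% is the power of a comparison of single-time levels with no patients lost. Whether it also describes the slope comparison depends on a correlation that the article does not give. Across an assumed ρ of 0.3 to 0.8, power for a 20% change ranges from about 39% to 89% with 33 per arm and from about 32% to 80% with 26. For a 10% change it stays at about 35% or below throughout, so the admission of low power is sound for the change that the protocol calls clinically significant. If the withdrawn patients' data are lost, the protocol's own SD of 0.3 gives about 14%/42%. These results assume 1:1 allocation, a two-sided test, equal SDs at the two visits, complete data in those analysed and no covariate adjustment.

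**What to change.** In the Power calculation section, restate the power for the rate of change in pentraxin 3, using SD 0.3 × √(2(1 − ρ)), over a stated range of ρ such as 0.3 to 0.8, and label ρ as an assumption. Give the number per arm behind each figure, and say whether patients who withdraw are counted through continued follow-up (33 per arm) or treated as lost (26 per arm). The table above can serve as it stands.

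The cost is a few lines of wording. Sample size, treatment, visits and analysis are untouched. The drawback is that one figure becomes a range.

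### The stated 17% and 52% power for pentraxin 3 belong to an unadjusted 0.05 test; under the planned Holm correction they are upper bounds

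*Protocol article*

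**What the plan says.** The protocol article names three primary outcomes in the Abstract, in the primary objectives section and in Table 2: aortic pulse wave velocity (PWV), plasma isoprostanes and plasma pentraxin 3. The hypotheses are that all three improve.

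The Power calculation section sets the sample size by feasibility: "Resource limitations will allow us to recruit 66 patients within a two-year period". It takes pentraxin 3 as the most variable outcome, with "pentraxin 3 = 0.75 ± 0.3", regards a 10% fall as clinically significant, and reports: "Therefore, with alpha = 0.05, we will have about a 17% power to detect this 10% change in pentraxin 3", with 52% for a 20% change. It adds: "This also allows for a 20% withdrawal rate". It admits that power is small and does not mention multiplicity.

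The Statistical analysis section compares the mean rate of change in the primary outcomes between groups by general linear modelling and then has "P-values corrected for multiple comparisons by the Holm method". It does not say which P-values form the Holm family.

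**The concern.** The two sections describe different tests. Holm over three outcomes compares the smallest P-value with 0.05/3 = 0.0167, the next with 0.05/2 = 0.025 and the largest with 0.05, and stops at the first failure. Pentraxin 3 therefore gets the 0.05 used in the power calculation only when PWV and isoprostanes have both been declared significant. In every other case it faces a stricter threshold or is not tested further.

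The power figure does not set the sample size here. Its use is to tell readers how much weight a null pentraxin 3 result can bear, and to inform the follow-on study that the section mentions. For both uses, the quoted power should be that of the test actually planned, or be labelled as something else.

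**Working it through.** **Inputs.** All are from the Power calculation section unless noted.
- Pentraxin 3: mean 0.75, SD 0.3. A 10% change is 0.075, or 0.075/0.3 = 0.25 SD; a 20% change is 0.15, or 0.5 SD.
- SD/mean: isoprostanes 7.0/54.1 = 0.129; PWV 2.4/11.4 = 0.211; pentraxin 3 0.3/0.75 = 0.40.
- 66 patients. The allocation ratio is not stated; 1:1, so 33 per arm, is assumed.
- Sidedness is not stated; two-sided is inferred in step 1.
- Holm family: the three primary outcomes, one test each (inferred from the Statistical analysis section).

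**Formula.** Two-sample t test with n per arm and standardised effect d: noncentrality = d × √(n/2), df = 2n − 2, power = P(|noncentral t| > two-sided critical value at alpha).

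**Step 1: reproduce the stated figures.** With n = 33, √16.5 = 4.062, so the noncentrality is 1.016 (10%) and 2.031 (20%), with df = 64. At two-sided alpha 0.05 the power is 17.0% and 51.6%, matching the stated 17% and 52%. One-sided 0.05 gives 26% and 64%, which does not match. The stated figures therefore contain no multiplicity adjustment.

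**Step 2: bounds under Holm.** A P-value at or below 0.0167 is always rejected by Holm over three tests, and one above 0.05 never is. So, whatever the other outcomes do, pentraxin 3 power lies between its power at 0.0167 and its power at 0.05.

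| Two-sided alpha, 33 per arm | 10% change | 20% change |
|---|---|---|
| 0.0167 (first step) | 8.1% | 34.2% |
| 0.025 (second step) | 10.7% | 40.1% |
| 0.05 (last step) | 17.0% | 51.6% |

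**Step 3: where between the bounds.** The full Holm procedure was simulated with t tests, the protocol's own means and SDs, 33 per arm, and correlation between outcomes of 0 to 0.5.

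| Scenario | Pentraxin 3 power | Stated |
|---|---|---|
| Only pentraxin 3 changes, by 10% | about 8% | 17% |
| All three change by 10% | 12% to 14% | 17% |
| Only pentraxin 3 changes, by 20% | about 34% | 52% |
| All three change by 20% | about 51% | 52% |

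A normal approximation gives slightly higher values (8.5%, 12.6% to 14.6%, 36%, 52%) and the same pattern.

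The standardised effects explain it. If all three change by 20%, isoprostanes move by 0.2/0.129 = 1.55 SD and PWV by 0.2/0.211 = 0.95 SD. Both are nearly always rejected, and pentraxin 3 is then tested at 0.05. If all three change by 10%, the effects are 0.77 and 0.47 SD. PWV is rejected in only a little over a third of trials, so pentraxin 3 often does not reach the last step.

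**Step 4: after withdrawal.** 66 × 0.8 = 52.8, about 26 per arm. At 0.0167 the power is 6.5% and 26%; at 0.05 it is 14% and 42%. The fall from 17% and 52% to 14% and 42% comes from withdrawal alone. It is a separate discrepancy: the stated figures reproduce only with all 66 patients, although the text says they allow for 20% loss.

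**The case against.** The strongest reply is that Holm is not a flat division by three. The protocol expects all three outcomes to improve, and pentraxin 3 was chosen for the power statement because it is the most variable. With equal percentage changes it tends to have the largest P-value, which Holm tests at 0.05. This stands for the 20% figure: if all three change by 20% in the full sample, power is about 51% and the stated 52% is essentially right. It only partly stands for the 10% figure, where the same expectation gives 12% to 14%, still 3 to 5 points below 17%.

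A reader might infer that the true power is simply 8% and 34%, so that the first figure is halved and both are plainly wrong. The documents do not support that. Those values are the floor, reached in effect when the other two outcomes do not respond, which is not what the trial hypothesises. Nor is there a calculation error: 17% and 52% are correct for the unadjusted test.

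Three further points have weight. The Holm family is inferred, so the exact figures depend on that reading; a wider family would lower power further. The sample size is fixed by resources and low power is openly conceded, so no design decision rests on 17%, and Holm as written still controls the type I error. Finally, the larger trial foreseen in the Abstract and Discussion would assess cardiovascular morbidity and mortality, so it would probably not be sized from a pentraxin 3 figure, and a null result would be read largely from its confidence interval. These points limit the consequence. They do not make the power section agree with the analysis section: conceding that power is small does not tell the reader that the quoted figures are best cases.

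**Conclusion.** The point holds as an inconsistency between two sections. The stated 17% and 52% are unadjusted single-outcome power, and under Holm over the three primary outcomes they are upper bounds. With all 66 patients, the range for pentraxin 3 is about 8% to 14% for a 10% change and 34% to 51% for a 20% change, over the scenarios examined. The 17% would be approached only if rejection of both other outcomes were almost certain, which a 10% change in each does not deliver.

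This rests on 1:1 allocation, two-sided tests, a Holm family of exactly the three primary outcomes, correlations of 0 to 0.5, and the protocol's cross-sectional SDs. The planned test compares rates of change, whose SD is not given, so that effect cannot be computed.

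Severity is moderate to minor: the trial is badly underpowered for a 10% change on either figure, and the sample size is unaffected.

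**What to change.** In the Power calculation section, label 17% and 52% as unadjusted upper bounds and add the Holm first-step (0.0167) lower bounds of about 8% and 34%. If the 20% withdrawal allowance is kept, give both bounds on about 26 per arm: 6.5% to 14% for a 10% change and 26% to 42% for a 20% change, and note that the drop in the upper bounds corrects the separate withdrawal discrepancy.

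In the Statistical analysis section, state that the Holm family is the three primary outcomes, with one test each.

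The cost is wording only. The sample size, the tests and the error control stay as they are; the stated power becomes less favourable.

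### The stated 17% and 52% power assume all 66 patients are analysed, so they do not allow for 20% withdrawal

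*Protocol article*

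**What the plan says.** All the inputs are in the protocol article, Power calculation section, apart from a confirming line in the abstract.

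- The sample size is set by resources: "Resource limitations will allow us to recruit 66 patients within a two-year period". The abstract (Method and Design) agrees: "A total of 66 renal transplant recipients will be enrolled". Both describe patients entering the trial, not patients completing it.
- Pentraxin 3 is chosen as the most variable of the three primary outcomes, with "pentraxin 3 = 0.75 ± 0.3".
- The smaller target effect is justified clinically: "We assume that a decrease of 10% in pentraxin 3 would be clinically significant". A 20% change is given as a second scenario.
- The result, "with alpha = 0.05", is: "we will have about a 17% power to detect this 10% change in pentraxin 3 and a 52% power to detect a 20% change".
- The next sentence reads: "This also allows for a 20% withdrawal rate". The section then concedes that power is small and presents the trial as groundwork for a larger one.

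The section does not name the test, its sidedness, the allocation ratio, a correlation between visits or an SD of change.

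**The concern.** A power figure that allows for withdrawal must be computed on the number expected to be analysed. With 66 entering and 20% lost, that is about 53. If the figures were computed on 66, the allowance was not made and the sentence claiming it is untrue.

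The stakes are limited but real. The percentages are the protocol's only statement of what the trial can detect. A reader weighing a null result would take the chance of detecting a 20% change to be about one in two even after the expected losses. Anyone planning the follow-on trial could also take 66 as a number already inflated for dropout and carry the error forward.

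**Working it through.** **Inputs**

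- Patients entering: 66 (Power calculation; abstract). With 1:1 allocation (assumed), 33 per arm.
- Mean 0.75, SD 0.3, alpha 0.05 (Power calculation). Two-sided (assumed).
- 10% change: 0.10 × 0.75 = 0.075, so d = 0.075 / 0.3 = 0.25.
- 20% change: 0.20 × 0.75 = 0.15, so d = 0.15 / 0.3 = 0.50.
- After 20% withdrawal: 66 × 0.8 = 52.8, or 26.4 per arm, so 26 to 27.

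**Formula.** For n per arm, the noncentrality parameter is d × √(n/2). Power is the probability that a noncentral t variable with 2n − 2 degrees of freedom falls beyond the two-sided 5% critical values. The normal approximation is Φ(d√(n/2) − 1.96).

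**Step 1: reproduce the stated figures.** With n = 33, √(33/2) = 4.062.

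- d = 0.25: noncentrality 1.016. Normal: Φ(−0.944) = 17.3%. Exact t: 17.0%. Stated: 17%.
- d = 0.50: noncentrality 2.031. Normal: Φ(0.071) = 52.8%. Exact t: 51.6%. Stated: 52%.

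Both figures are reproduced with no withdrawal.

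**Step 2: solve back for n.** A power of 17% at d = 0.25 needs 32.4 (normal) to 33.0 (t) per arm. A power of 52% at d = 0.50 needs 32.3 (normal) to 33.3 (t) per arm. The two figures separately point to about 33 per arm, the full 66.

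**Step 3: apply the 20% withdrawal.** With n = 26, √(26/2) = 3.606, so the noncentralities are 0.901 and 1.803.

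| Analysed per arm | 10% change, t | 10% change, normal | 20% change, t | 20% change, normal |
|---|---|---|---|---|
| 33 (no loss) | 17.0% | 17.3% | 51.6% | 52.8% |
| 27 | 14.7% | 14.9% | 43.8% | 45.1% |
| 26.4 | 14.5% | 14.6% | 43.0% | 44.3% |
| 26 | 14.3% | 14.5% | 42.4% | 43.8% |

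Against the stated 52%, the shortfall is 52 − 45 = 7 to 52 − 42 = 10 points. Against the stated 17%, it is 2 to 3 points.

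**Step 4: is the test one-sided?** By exact t, a one-sided test at 26 per arm gives 22.5% and 55.3%; at 33 per arm it gives 26.1% and 64.2%. Neither pair matches 17% and 52%.

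**Step 5: what would make the sentence true?** 66 / 0.8 = 82.5, so about 83 recruited. At 83 × 0.8 = 66.4 analysed, exact t gives 17.1% and 51.9%. The protocol puts its recruitment ceiling at 66.

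**The case against.** The strongest reply is that the section does not name its model. The Statistical analysis section compares per-patient rates of change, not a single cross-sectional value, and some change-type models do return about 17% and 52% after the loss:

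- A change score with correlation 0.6 between visits, at 26.4 per arm, gives 16.9% and 51.3%. That correlation makes the variance factor 2(1 − 0.6) = 0.8, which exactly cancels a 20% loss.
- Baseline adjustment with a correlation of about 0.45 gives 17.0% and 51.4% at 26.4 per arm.
- An SD that falls in proportion to the mean gives 16.0% and 52.7% at 27 per arm (normal approximation).

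So the error is inferred from the match, not read directly off the page. But each of these models needs an input that the section never gives, while the plain calculation on the one mean and SD it does give reproduces both figures unaided. If another model was used, the section must say so, and the text needs correcting either way.

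A second reply is that patients who withdraw will be asked to agree to continued testing (Withdrawal from Study). That may reduce the loss, but it does not put an allowance into a figure computed on all 66.

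Three points on the other side stand. The 10%-change gap is small for a figure given as approximate, so the evidence rests mainly on the 52% and on the solved-back n. The sample size came from resources and the protocol already admits low power, so no design decision turns on the correction. And the restated figures, like the stated ones, use an unadjusted 0.05, although the analysis applies Holm's correction. If that covers the three primary outcomes, the first step at 0.05/3 gives about 26% for a 20% change at 26 per arm.

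**Conclusion.** The concern holds. On the protocol's own inputs, 17% and 52% are the powers with all 66 patients analysed, and the claim that they allow for 20% withdrawal is wrong as written. With that withdrawal, power is about 14% for a 10% change and about 42% for a 20% change (26 per arm, exact t). Across 26 to 27 per arm and both methods, the ranges are 14–15% and 42–45%.

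This assumes a two-sided test, 1:1 allocation and a comparison of means with SD 0.3. The practical effect is modest, since the trial is underpowered on either set of figures and says so. What has to go is the specific assurance that the stated power survives the expected loss.

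**What to change.** Delete the withdrawal sentence and restate the power along these lines:

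> With 66 randomised and 20% withdrawal (about 26 per arm analysed), a two-sided two-sample t-test at 0.05 has about 14% power for a 10% change in pentraxin 3 and about 42% for a 20% change; 17% and 52% apply only if all 66 complete.

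Naming the test, as here, removes the ambiguity about the model. If the original calculation did use a change score or baseline adjustment, give its correlation or SD of change and its source instead. It would also help to say that these figures precede the Holm correction.

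The cost is one sentence of wording and a less favourable stated power. It needs no extra patients and no change to design or analysis. Keeping 17% and 52% after 20% loss would instead take about 83 recruited, above the stated ceiling of 66.
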